### Population and sample size calculation

2.4

Fifty-four patients undergoing planned surgical treatment for IE will be randomly allocated (1:1 allocation) to receive either best standard of care plus cytokine adsorption (protocol A) or best standard of care alone (protocol B). Allocation to the groups, protocol A or protocol B, is done computerized using the REDCap software. The null hypothesis is that there is no differences in mHLA-DR expression (readout: monoclonal antibodies [mAb/cell]) between the 2 groups. Assuming the response to be normally distributed within each subject group with a standard deviation of 3200 mAb/cell and a true difference in the arms means of 2500 mAb/cell (10,000 vs 7500 mAb/cell of mHLA-DR expression), n = 27 patients will be required to be able to reject the null hypothesis that the population means of the experimental and control groups are equal with probability (power) of 0.8. The type I error probability associated with this test of this null hypothesis is 0.05 (2 sided).

The following inclusion criteria apply:

1.Subjects scheduled for cardiac surgery for infectious endocarditis (according to DUKE criteria) with antibiotic therapy for ≤14 days.2.Presence of informed consent3.Age ≥18 years.

The following exclusion criteria apply:

1.Known previous treatment (last 6 months) with immunologically active biologicals or specific immunomodulatory drugs (e.g., rituximab).2.Known high-dose chronic (i.e., before onset of infectious endocarditis) steroid medication with prednisone equivalent of >30 mg/day.3.Patients on extracorporeal membrane oxygenation (ECMO), or any other (preoperative) cardiac assist device.4.Moribund patient (life expectancy <14 days, as judged by investigator).

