#### Secondary endpoints

2.5.3

1.Change in mHLA-DR from baseline (pre-OP) to post-OP (visit 4) and day 3 (visit 5) post-OP.2.Area under the curve (AUC) of quantitative mHLA-DR expression between baseline (pre-OP), ICU admission, and days 1 (visit 4) and 3 (visit 5) post-OP.3.Change in inflammatory markers including cytokines (including white blood count, C-reactive protein, interleukin 6 [IL-6], IL-10, multiplex enzyme-linked immunosorbent assay, inflammatory markers) and immune cell phenotype (flow cytometry) from pre-OP to days 1 (visit 4) and 3 (visit 5) post-OP.4.Change in organ dysfunction (Sequential Organ Failure Assessment scores including subscores) from baseline (pre-OP) to days 1 (visit 4) and 3 (visit 5) post-OP.5.Length of ICU/hospital stay (days after ICU admission) and total days in hospital.6.Cumulative Therapeutic Intervention Scoring System (TISS) points (resource need) while on ICU.7.ICU-, hospital-, 28-day, 60-day, and 90-day mortality.8.Total amount of infused fluids on ICU; including number and type of transfusions.9.Duration of vasoactive drug therapy, cum. vasopressor dose.10.Length of invasive mechanical ventilation (intubation to extubation), renal function (secondary) ECMO, or other circulatory supporting systems.

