We will provide descriptive statistics for, for example, length of ICU and hospital stay (days after surgical interventions), and cumulative TISS points (resource need) and compare groups by the nonparametric Wilcoxon-Mann-Whitney test. We will show proportions of ICU mortality, hospital mortality, and 28-day mortality and compare groups calculating a risk difference and applying a chi-square test.

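### ICU stay, hospital stay and cumulative TISS get a valid but unadjusted Wilcoxon test, although the planned pre-operative SOFA score could serve as a covariate and may add precision

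*Protocol article*

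**What the plan says.** Section 2.8 (Analysis of results) gives descriptive statistics for ICU stay, hospital stay and cumulative TISS points and will "compare groups by the nonparametric Wilcoxon-Mann-Whitney test". No covariate is named for these outcomes.

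A severity score before treatment is planned. The fourth secondary endpoint in section 2.5.3 is "Change in organ dysfunction (Sequential Organ Failure Assessment scores including subscores) from baseline (pre-OP", followed to postoperative days 1 and 3. Section 2.7 adds that routine clinical and laboratory data are used to assess organ function where they are available.

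Other analyses in section 2.8 do adjust. The primary linear model is corrected for baseline mHLA-DR, and the mixed models for mHLA-DR, inflammatory markers and organ dysfunction include a baseline value as a covariate.

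On size and allocation, section 2.4 says: "Fifty-four patients undergoing planned surgical treatment for IE will be randomly allocated (1:1 allocation"), by computer. The article mentions no stratification by severity.

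**The concern.** Length of stay and cumulative TISS plausibly depend on how ill the patient was before surgery. Section 2.4 admits adults scheduled for endocarditis surgery and excludes, on grounds of severity, those judged moribund and those on ECMO or another cardiac assist device. That leaves room for wide variation. If pre-operative SOFA predicts these outcomes, a two-sample rank test leaves the explained variation in the noise, and a SOFA-adjusted comparison would be more precise with no new data collected.

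At stake is the information the pilot yields on resource use. The Discussion says the findings should be confirmed in multicentre studies, and a more precise comparison would help in planning them.

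**Working it through.** **1. The plan's own figure.** Section 2.4 assumes a "standard deviation of 3200 mAb/cell" and a "true difference in the arms means of 2500 mAb/cell (10,000 vs 7500 mAb/cell of mHLA-DR expression"), with power 0.80 and a two-sided alpha of 0.05. The standardised effect is 2500/3200 = 0.78. By normal approximation, n per arm = 2 × (1.960 + 0.842)² × (3200/2500)² = 2 × 7.849 × 1.638 = 25.7, so 26. The t-test version gives 26.7, so 27, with power 0.804 at 27. The stated 27 per arm reproduces. It concerns mHLA-DR only; stay and TISS are not powered.

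**2. Inputs for the check.** From the documents: 27 per arm and two-sided alpha 0.05. Assumed, because the documents do not give them: the correlation r between pre-operative SOFA and the outcome, varied from 0 to 0.6, and the size of the treatment shift (0.6 SD, and 0.78 SD as a second case).

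**3. Theoretical gain.** Adjusting for a covariate with correlation r multiplies the variance of the treatment comparison by 1 − r²: 0.99, 0.96, 0.91, 0.84, 0.75 and 0.64 at r = 0.1 to 0.6. The extra parameter costs about 2% (factor 1 + 1/50). The net factor is therefore 0.99 × 1.02 = 1.01 at r = 0.1 (a slight loss), 0.98 at r = 0.2 and 0.86 at r = 0.4.

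**4. Simulated power.** Skewed outcome (an exponentiated normal variable), SOFA rounded and bounded at 0 to 24, 27 per arm; Wilcoxon test against ANCOVA on ranks with arm and SOFA.

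| r | 0.6 SD: Wilcoxon | 0.6 SD: rank ANCOVA | 0.78 SD: Wilcoxon | 0.78 SD: rank ANCOVA |
|---|---|---|---|---|
| 0 | about 0.55 | no difference | 0.77 | 0.77 |
| 0.2 | 0.56 | 0.57 | 0.79 | 0.80 |
| 0.3 | about 0.55 | 0.59 | 0.77 | 0.80 |
| 0.4 | about 0.55 | 0.61 | 0.77 | 0.83 |
| 0.5 | about 0.55 | 0.64 | 0.76 | 0.86 |
| 0.6 | about 0.55 | 0.71 | 0.77 | 0.91 |

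The 0.78 SD columns rest on 4,000 trials per setting, so a power near 0.77 has a Monte Carlo standard error of √(0.77 × 0.23/4000) = 0.007. Differences of 0.01 are noise.

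**5. Type I error.** With no treatment effect, the Wilcoxon test rejected in 0.044 to 0.049 of trials and the rank ANCOVA in 0.041 to 0.056. The Monte Carlo standard error is √(0.05 × 0.95/4000) = 0.0034, so both are close to 0.05.

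**6. Chance imbalance.** The between-arm difference in mean SOFA, in SD units, has a standard deviation of √(2/27) = 0.27. It exceeds 0.3 SD with probability 0.27 and 0.5 SD with probability 2 × P(Z > 0.5/0.272) = 0.066.

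**7. Gain expressed as patients.** The textbook figure 1/(1 − r²) gives 1.10, 1.19, 1.33 and 1.56 at r = 0.3 to 0.6. This is too generous here. A plain Wilcoxon test with that many patients (30, 32, 36 and 42 per arm) had simulated power 0.61, 0.63, 0.69 and 0.75, above the 0.59, 0.61, 0.64 and 0.71 of the rank ANCOVA with 27. At r = 0.6, moving from power 0.55 to 0.71 corresponds to ((1.960 + 0.553)/(1.960 + 0.126))² = 1.45, or about 45% more patients instead of 56%.

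**The case against.** The strongest reply is that nothing is wrong with the planned test. Wilcoxon-Mann-Whitney is a standard choice for skewed stay and score data, and its type I error holds. That stands. A reader might infer that uncorrected chance imbalance biases the comparison; it does not, because randomisation already allows for such imbalance in the error rate.

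A reader might also see an inconsistency with the adjusted analyses elsewhere in section 2.8. The documents do not support this. Those analyses adjust for a baseline value, in the primary model the outcome's own. Stay and TISS have no baseline of their own, so SOFA would be a further choice of prognostic covariate.

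It is also tempting to say that every patient has a SOFA score and that precision is simply being thrown away. The score is planned, but the article does not say it will be complete, and section 2.7 makes the use of routine data conditional on availability. The gain depends on a correlation the documents do not give.

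Finally, an article may leave covariates to a fuller plan. That reply is weaker here: the article does fix a method for these outcomes, and the point is about that method, not about a missing detail. The absence of a described stratification, by contrast, may be mere condensation, and nothing here depends on it.

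**Conclusion.** The point holds as an efficiency improvement. The article fixes an unadjusted test for three outcomes while planning to collect a plausible prognostic covariate. The benefit is negligible at a correlation of 0.2 or below and becomes material from about 0.4. Under the assumed 0.6 SD shift, power rises from about 0.55 by roughly 0.04 at a correlation of 0.3 and 0.16 at 0.6. If SOFA proves uninformative, the cost is close to nil.

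These figures rest on the assumed shift, the assumed correlations, the simulated outcome shape and complete SOFA data. They were obtained for rank ANCOVA; a proportional-odds model was not simulated. The outcomes are secondary and unpowered in a self-described pilot, and power is modest with or without adjustment in most of the range. The primary analysis, the sample size and the main conclusion are unaffected. Priority is low, but the change is cheap.

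**What to change.** In section 2.8, or in the analysis plan it refers to, prespecify for ICU stay, hospital stay and cumulative TISS:

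- a rank ANCOVA of the outcome on arm and pre-operative SOFA; or, if an adjusted odds ratio with a 95% confidence interval is wanted, a proportional-odds model with the same terms;
- with the proportional-odds model, a direct assessment of that assumption. The Wilcoxon test cannot serve as the check, because it is essentially the score test of the same model without the covariate;
- a simple imputation rule for missing baseline SOFA, blind to arm (for example the median of all observed baseline values, both arms pooled), so that no randomised patient is dropped for want of the covariate;
- the unadjusted Wilcoxon test reported alongside.

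Naming the covariate in advance also rules out choosing it after an imbalance has been seen. The cost is a change of wording, one extra model assumption and one degree of freedom; no new data are needed.

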## Discussion

3

Previous data show that functional impairment of cell-mediated immunity reflects an additional “organ” dysfunction in the context of life-threatening injury, such as severe infection.^3^,^5^,^17^ Although large-scale clinical data are missing, IE is known to trigger several humoral and immune cellular pathways, often resulting in a state of immunosuppression in affected individuals, and this was shown of prognostic importance in critically ill patients.^3^,^18^

In the current investigator-driven clinical study RECReATE, we aim to analyze the impact of a cytokine removal strategy (1 treatment session during cardiopulmonary bypass) on key humoral and cellular immune response mechanisms. In brief, we strive to explore whether cytokine adsorption can increase (or even restore) monocytic immune competence (assessed by mHLA-DR expression) in surgically treated patients with IE. Data from previous clinical studies investigating immunostimulatory^[10]^ and selective extracorporeal cytokine removal strategies^[11]^ demonstrate that monocytic function (mHLA-DR-expression) can be restored using comparable measures. Thus, it seems likely that treatment using this alternative cytokine removal strategy will result in increased mHLA-DR expression, reflecting improved monocytic immune function.

Our study has a number of limitations that deserve discussion. First, this is a single-center pilot study with inherent limitations (including limited external validity) set by the chosen study design. Findings in this pilot study should therefore be confirmed in subsequent multicentre investigations. Importantly, however, the primary endpoint is assessed using a standardized quantitative assay with an adequate inter- (and intra-) coefficient of variation shown in multinational comparison studies.^[8]^ Second, although the sample size appears rather limited in this pilot study, it might be considered a strength of the current analysis that the sample size calculation/ power regarding the primary endpoint was partly based on data from respective previous clinical studies. Third, optimal “dose” of the cytokine adsorption applied is currently unknown and, theoretically, one might speculate that the applied “adsorption dose” (treatment only while patients are on cardiopulmonary bypass) might be insufficient. However, this best reflects current practice, in which physicians might chose to prescribe cytokine adsorption based on personal preference.

In conclusion, this pilot trial will answer the important question of whether cytokine adsorption during cardiopulmonary bypass will result in increased mHLA-DR expression, a recognized global functional immune marker. Novel therapeutic approaches seem urgently required in critically ill patients and data from this pilot study will allow to explore new innovative immunomodulatory strategies.
